### Radiation therapy, process of PT/HIT

All patients with osteosarcoma who meet the above mentioned criteria will be included. Chemotherapy prior and after HIT is recommended according to standard therapy protocols like EURAMOS1 and is not part of this trial protocol.

PT and HIT will be administered at the Department of Radiotherapy of Heidelberg University at least one week after the last chemotherapy cycle, if the inclusion criteria have been met. HIT will be given mainly on an outpatient basis on 5-6 days per week but with daily clinical examinations by a radiotherapist respectively by a pediatrician. Necessity of inpatient basis has to be verified individually for example in case of adverse events during PT/HIT. Then the treatment will be arranged and supervised by the Department of Pediatric Oncology, Hematology, Immunology and Pneumology of the Heidelberg University.

No treatment other than PT/HIT may be administered during PT/HIT.

After the end of PT/HIT, adjuvant chemotherapy can be continued within one week according to standard therapy protocols, e.g. according to EURAMOS 1 trial arm "poor response" (figure 1).

**Figure 1 F1:**
[figure not shown]
**Chronological course of the therapy trial**. HIT/PT will be administered at least one week after the last chemotherapy cycle on 6 days per week. Chemotherapy prior and after HIT/PT is recommended according to standard therapy protocols and is not part of this trial protocol. After the end of HIT/PT, adjuvant chemotherapy can be continued within one week. Diagnostic investigations have to be done at a specific date pre and after HIT/PT. FDG-PET characteristics will be evaluated prospectively.

### Technique

Patients will be rigidly immobilized to ensure a high repositioning accuracy of the tumor region and adjacent structures for PT/HIT. Set-up deviations larger than > 1 mm in the skull base region and larger than 3 mm in the spinal and pelvic region will be corrected prior to each irradiation. If necessary, children will be anesthetized for the procedure.

The planning target volume results from the clinical target volume plus a safety margin that depends on tumor site and immobilization technique.

GTV (Gross Tumour Volume) is delineated according to MRI/CT-Scan/PET-CT.

CTV(Clinical Target Volume) contains the visible GTV + the subclinical microscopic malignant disease. The original (pre-chemotherapy, pre-operative) tumour extension should guide the CTV-delineation. In axial tumours a clinical safety margin of 2 cm added to the GTV should be attempted. For extremity sarcomas a margin of 4-5 cm around the GTV is preferred.

PTV (Planning Target Volume) is delineated in collaboration with the radiation-physicist taking into account organ and patient movement as well as inaccuracies in beam and patient set-up.

Organs at risk such as rectum, bladder, femoral heads, central nerves, spinal cord are contoured.

The quality of patient immobilization will be checked quantitatively daily via digital x-ray equipment. During HIT, set-up is checked daily with a system based on orthogonal x-ray devices and set-up deviations >1 mm for skull base tumors and >3 mm for pelvic/spinal/extremity tumors are corrected prior to PT/HIT.

### Treatment planning

Treatment planning includes biological plan optimization using the local effect model (LEM), which is included into the treatment planning software. Active beam delivery using the raster scan system is used to spare normal tissue surrounding the tumor. Desired target dose is 60-66 Cobalt Gray Equivalent (Gy E), whenever possible. It is applied through 1 - 3 isocentric treatment portals via proton therapy plus a heavy ion boost of 15-21 GyE. Dose distributions are calculated and dose volume histograms (DVH) are generated. A α/β-ratio of 2 is used for biological plan optimization. Fractionation is planned to be equivalent to 5 × 2 Gy PT per week and 5-6×/3 Gy E HIT per week. Dosage to organs at risk is minimized.

### Duration of Therapy

Treatment continues for **20 to 40 days **or until one of the following criteria applies:

▪ Other illness that prevents further administration of treatment,

▪ Patient or legal guardian decides to withdraw from the study, or

▪ General or specific changes in the patient's condition render the patient unacceptable for further treatment in the judgment of the investigator.

Because the tumors of the patients who are eligible to be included in this study will not be resectable, the regression grade following chemotherapy cannot be determined according to standard criteria. A recent study showed significant alterations of glucose-uptake in FDG-PET of osteosarcoma after response to chemotherapy, which correlated with the histopathologic assessment of response [10-12]. Therefore, in this study FDG-PET will be used for the prospective evaluation of tumor response after PT/HIT. If possible, FDG-PET will be performed before start of neoadjuvant chemotherapy. FDG-PET has to be performed obligatory no more than one week before the initiation of PT/HIT (week 10), after PT/HIT (week 15), at the end of the complete tumor therapy (week 30) and 6 months after tumor therapy (figure 1).

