**Methods/Design:**

This is a monocenter, single-arm study for patients ≥ 6 years of age with non-resectable osteosarcoma. Desired target dose is 60-66 Cobalt Gray Equivalent (Gy E) with 45 Gy PT (proton therapy) and a carbon ion boost of 15-21 GyE. Weekly fractionation of 5-6 × 3 Gy E is used. PT/HIT will be administered exclusively at the Ion Radiotherapy Center in Heidelberg. Furthermore, FDG-PET imaging characteristics of non-resectable osteosarcoma before and after PT/HIT will be investigated prospectively. Systemic disease before and after PT/HIT is targeted by standard chemotherapy protocols and is not part of this trial.

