#### Prospective Evaluation of Fluorodeoxy-D-Glucose Positron Emission Tomography (PET)

A secondary objective of this study is to describe the FDG-PET imaging characteristics in patients with osteosarcoma before and after HIT and to determine the association between FDG-PET and survival respectively time to progression.

FDG-PET has to be performed obligatory at 4 time points: one week before start of PT/HIT, after PT/HIT, at the end of complete tumor therapy and 6 months after PT/HIT. If possible, FDG-PET has to be performed initially before start of neoadjuvant therapy.

Results, respectively response criteria will be evaluated in future.

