### Follow-up

Follow-up visits are obligatory 1 week, 6 and 19 weeks, as well as 6, 12, 24, 36 48 and 60 months after PT/HIT. For a detailed plan of follow-up diagnostics see table 1.

**Table 1 T1:** Obligatory Assessment after HIT/PT

	Visit Department of Radiooncology, Heidelberg	Physical Examinations and Blood Tests	Chest X-ray	Chest CT-Scan	X-ray of Primary Tumor Site or Skeletal Metastases	CT/MRI of Primary Tumor Site or Skeletal Metastases	Whole Body FDG-PET	Whole Body Tc99 bone scan
Week 14	X	X					X	
Week 19	X	X	X	If chest x-ray shows strong suspicion of metastases	X	X		X
Week 33	X	X	X	If chest x-ray shows strong suspicion of metastases	X	X	X	X
6 months after PT/HIT	X	X	X	If chest x-ray shows strong suspicion of metastases	on clinical suspicion of metastases	X	X	on clinical suspicion of metastases
12 months after PT/HIT	X	X	X	If chest x-ray shows strong suspicion of metastases	on clinical suspicion of metastases	X	on clinical suspicion of metastases	on clinical suspicion of metastases
24, 36, 48 and 60 months after PT/HIT	X	X	X	If chest x-ray shows strong suspicion of metastases	on clinical suspicion of metastases	X	on clinical suspicion of metastases	on clinical suspicion of metastases

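### The obligatory FDG-PET schedule contradicts itself, and its fixed week numbers do not set a constant interval after the last PT/HIT fraction

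*Protocol article*

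**What the plan says.** Three places in the protocol article set the PET calendar.

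- **Duration of Therapy:** the baseline scan is tied to the start of PT/HIT and carries a week-10 label. The later scans are due "after PT/HIT (week 15), at the end of the complete tumor therapy (week 30) and 6 months after tumor therapy".
- **Prospective Evaluation of FDG-PET:** the same four occasions without week numbers, the last two being "at the end of complete tumor therapy and 6 months after PT/HIT".
- **Follow-up, Table 1**, titled "Obligatory Assessment after HIT/PT": PET is marked at Week 14, at Week 33 and at 6 months after PT/HIT.

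The visit text reads "Follow-up visits are obligatory 1 week, 6 and 19 weeks, as well as 6, 12, 24, 36 48 and 60 months after PT/HIT". Adverse events gives the same visits. Table 1 labels its first three rows Week 14, Week 19 and Week 33.

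The length of treatment comes from several statements:

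- The abstract gives "45 Gy PT (proton therapy) and a carbon ion boost of 15-21 GyE" with 5-6 fractions of 3 GyE a week.
- Treatment planning says "Fractionation is planned to be equivalent to 5 × 2 Gy PT per week and 5-6×/3 Gy E HIT per week".
- The Figure 1 caption has treatment on 6 days a week.
- Duration of Therapy states 20 to 40 days.

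**The concern.** Describing PET before and after PT/HIT, and relating it to survival and time to progression, is a stated secondary objective. Duration of Therapy also relies on PET to evaluate response after PT/HIT, because histological regression cannot be graded in these tumors. Both uses need a known interval between the last fraction and the scan.

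The passages give different weeks for the same scan and different anchors for the last one. Because the length of treatment varies, a fixed week number does not fix that interval in any case. With 20 patients, avoidable variation in scan timing is hard to average out.

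**Working it through.** **1. The plan's own duration figure.** Doses are 45 Gy PT plus 15-21 GyE carbon, 60-66 GyE in total.

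- Treatment planning: 45/2 = 22.5, so 22 or 23 PT fractions. 15/3 = 5 to 21/3 = 7 carbon fractions. Total 27-30.
- 30 fractions at 5 a week from a Monday start finish on day 40, which reproduces the stated upper limit.
- The lower limit of 20 is not reproduced as calendar days. It equals the number of treatment days if the whole course is given in 3 GyE fractions (60/3 = 20), which is one reading of the abstract.

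**2. Week in which PT/HIT ends.** End week = start week + floor((days - 1)/7). The week-10 label could mark the baseline scan or the start of PT/HIT, so both starts are shown.

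| Reading | Fractions | Calendar days | End, week-10 start | End, week-11 start |
|---|---|---|---|---|
| Treatment planning (PT 5/week, carbon 5-6/week) | 27-30 | 36-40 | 15 | 16 |
| Same fraction sizes, 6 days/week throughout (Figure 1 caption) | 27-30 | 31-34 | 14 | 15 |
| Abstract's 3 GyE for the whole course, 5-6/week | 20-22 | 23-30 | 13 (14 for 22 fractions at 5/week) | 14 (15) |
| Stated duration | not given | 20-40 | 12-15 | 13-16 |

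For a week-10 start and the stated duration, Week 14 lies between 14 - 12 = 2 weeks after the end week and 15 - 14 = 1 week before it. Week 15 lies between 15 - 12 = 3 weeks after it and the end week itself.

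**3. PET versions side by side.**

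| Scan | Duration of Therapy | PET section | Table 1 |
|---|---|---|---|
| First after PT/HIT | week 15 | no week | Week 14 |
| End of therapy | week 30 | no week | Week 33 (corresponding scan) |
| Last | 6 months after tumor therapy | 6 months after PT/HIT | 6 months after PT/HIT |

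**4. Size of the anchor conflict.** Take 6 months as 26 weeks.

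- From PT/HIT ending in week 13-15: 13 + 26 = 39 to 15 + 26 = 41.
- From tumor therapy ending in week 30-33: 30 + 26 = 56 to 33 + 26 = 59.
- Gap: 56 - 41 = 15 to 59 - 39 = 20 weeks.

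**5. What Table 1's weeks mean.** They cannot be weeks since PT/HIT, because Week 33 is listed before the 6-month row (about 26 weeks). As calendar weeks, set against the 1, 6 and 19-week visits, they give 14 - 1 = 13, 19 - 6 = 13 and 33 - 19 = 14. PT/HIT would then end in week 13-14, and Week 19 is about 6 weeks after it.

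**The case against.** The strongest reply is that the text anchors the assessments to events. Visits are set at 1, 6 and 19 weeks after PT/HIT, both PET passages call the first scan a scan after PT/HIT, and the end-of-therapy scan is defined by that event with week 30 only in brackets. Table 1 does not call Week 33 the end of therapy. Figure 1, which may define the week count, is not shown. This is one center, and the PET objective is secondary, with response criteria deferred.

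Much of this stands, and it rules out several stronger readings that a reader might infer.

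- **That the Week 14 PET falls during irradiation.** Under the Treatment planning fractionation and a week-10 or later start, it does precede the end. With a week-10 start and 6 treatment days a week throughout, it falls in the closing week. With the same start and 3 GyE for the whole course, it is usually after the end. The stated 20 to 40 days allows either.
- **That the visit text is a further, conflicting calendar.** It matches Table 1 to within one week. The hazard is the label: Week 19 in the table against 19 weeks in the text.
- **That scans will not be comparable, or that the first toxicity visit moves into the treatment period.** Conflicting passages do not show what staff will do, and Adverse events times its visits from PT/HIT without calendar weeks.

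The reply does not remove the contradictions. Figure 1 can agree with at most one version of each conflicting week, and an event anchor cannot settle the last scan, where the passages name two different events.

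**Conclusion.** The obligatory PET schedule is contradictory and should be corrected. The first post-treatment scan differs by 1 week, the end-of-therapy scan by 3 weeks (if Table 1's Week 33 PET is that scan), and the last by about 15 to 20 weeks because its anchor differs. Even with one set of weeks, a fixed Week 14 or 15 would not hold the interval from the last fraction constant. Under the Treatment planning fractionation (36-40 days), Week 14 comes before treatment ends.

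The supportable consequence is that post-treatment scans may not be comparable across patients for the secondary PET-survival and PET-progression objective. The primary feasibility and toxicity objective is not shown to be affected.

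The figures assume Monday starts without interruption, a week-10 start unless stated, and 26 weeks for 6 months. The anchor gap also assumes PT/HIT ending in week 13-15 and therapy ending in week 30-33.

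**What to change.** - Reconcile Duration of Therapy, the PET section and Table 1 into one calendar.
- Express post-treatment visits and the first post-treatment PET as time since the last PT/HIT fraction, and relabel Table 1's Weeks 14, 19 and 33 to match.
- Define the end-of-therapy PET by the actual end of therapy, not week 30 or 33. State whether the PET in Table 1's Week 33 row is that scan.
- Name one anchor for the six-month PET and use it in all three places. The sponsor has to say which was meant.
- Reconcile the fractionation, days-per-week and duration statements in the abstract, the Figure 1 caption, Treatment planning and Duration of Therapy. This review does not choose among them.

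The cost is a correction to text and one table. No scan or visit is added.

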### Measurement of response

Response and progression will be evaluated in this study using the new international criteria proposed by the Response Evaluation Criteria in Solid Tumors (RECIST) Committee [13]. Changes in the largest diameter (one-dimensional measurement) of the tumor lesions are used in the RECIST criteria.

#### Prospective Evaluation of Fluorodeoxy-D-Glucose Positron Emission Tomography (PET)

A secondary objective of this study is to describe the FDG-PET imaging characteristics in patients with osteosarcoma before and after HIT and to determine the association between FDG-PET and survival respectively time to progression.

FDG-PET has to be performed obligatory at 4 time points: one week before start of PT/HIT, after PT/HIT, at the end of complete tumor therapy and 6 months after PT/HIT. If possible, FDG-PET has to be performed initially before start of neoadjuvant therapy.

Results, respectively response criteria will be evaluated in future.

### Time plan for the study

The study will be started in January 2010. Patient recruitment will be completed when 20 patients are included which is expected latest in 2015. Patient follow-up will continue for at least 5 years within our center, and will continue on a regular written basis (once yearly). The trial will be completed latest in 2020.

### Follow-up

Follow-up visits are obligatory 1 week, 6 and 19 weeks, as well as 6, 12, 24, 36 48 and 60 months after PT/HIT. For a detailed plan of follow-up diagnostics see table 1.

**Table 1 T1:** Obligatory Assessment after HIT/PT

	Visit Department of Radiooncology, Heidelberg	Physical Examinations and Blood Tests	Chest X-ray	Chest CT-Scan	X-ray of Primary Tumor Site or Skeletal Metastases	CT/MRI of Primary Tumor Site or Skeletal Metastases	Whole Body FDG-PET	Whole Body Tc99 bone scan
Week 14	X	X					X	
Week 19	X	X	X	If chest x-ray shows strong suspicion of metastases	X	X		X
Week 33	X	X	X	If chest x-ray shows strong suspicion of metastases	X	X	X	X
6 months after PT/HIT	X	X	X	If chest x-ray shows strong suspicion of metastases	on clinical suspicion of metastases	X	X	on clinical suspicion of metastases
12 months after PT/HIT	X	X	X	If chest x-ray shows strong suspicion of metastases	on clinical suspicion of metastases	X	on clinical suspicion of metastases	on clinical suspicion of metastases
24, 36, 48 and 60 months after PT/HIT	X	X	X	If chest x-ray shows strong suspicion of metastases	on clinical suspicion of metastases	X	on clinical suspicion of metastases	on clinical suspicion of metastases

### Monitoring

Monitoring is performed according to good clinical practice (GCP) guidelines. The monitoring and the data management will be performed by the Clinical Trial center of the Department of Radiation Oncology, University of Heidelberg.

## Discussion

Osteosarcoma is the most common bone tumor in children. Local control is absolutely critical concerning survival. Standard therapy protocols consist of surgical resection of the primary tumor and polychemotherapy. Until now, there has been no standard therapy protocol for non-resectable tumors.

For a long time, osteosarcoma was supposed to be a radioresistant tumor, but published small series of osteosarcoma patients have shown that radiotherapy with photons can achieve local control. However, a high radiation dose has to be applied, that usually cannot be given in non-resectable (mainly axial) tumors that are located close to critical organs like the brain, the spine or the bowels.

Particle therapy, respectively proton and carbon ion beams, have the advantage of a superior biological dose distribution that permits radiation with high doses even in the vicinity of critical organs. There is a steep dose fall-off after the so called "Bragg peak", which minimizes effects to normal tissue behind the Bragg peak. Furthermore, the relative biological effectiveness (RBE) of heavy ion beams within the Bragg peak is higher than that of photon beams and therefore has the potential advantage of providing a higher local effect in tumors that, like sarcomas, show low sensitivity to conventional radiation. Promising results have been obtained with HIT for a number of tumors in Japan as well as at the "Gesellschaft für Schwerionenforschung" (GSI) in Darmstadt, Germany. 3 year-local control rates of 73% for bone and soft tissue sarcomas were reported from the National Institute of Radiological Sciences in Japan [4,14]. At the GSI, high local control rates with minimal toxicity have been achieved for patients with chordomas and chondrosarcomas of the skull-base as well as adenoidcystic tumors [8]. From 2009, HIT will also be available at the University of Heidelberg. In contrast to other centres, the facility in Darmstadt (GSI) as well as the new facility in Heidelberg relies on active beam delivery using the so called raster scan technique, which offers physical advantages with better sparing of normal tissue in the entrance channel as well as less scattering dose. Moreover, the treatment planning procedure also includes biological plan optimization [15].

PT plus HIT seems to offer a new promising therapy option in patients with osteosarcoma little is known about side effects of HIT in children, but until now there is no curative alternative for inoperable osteosarcoma. Therefore, we have designed a phase I/II trial for patients with non-resectable osteosarcoma respectively patients who or whose legal guardians refuse local surgical resection. The purpose is to investigate the safety and toxicity of dose escalation via HIT as well as its efficacy in order to improve local control and outcome in these patients.

## Abbreviations

GYE: Cobalt Gray Equivalent; COSS: Cooperative Osteosarcoma Study; CT: Computertomography; CTC: Common Toxicity Criteria; DVH: Dose Volume Histogramm; EURAMOS: European American Osteosarcoma Study; FDG-PET: Fluorodeoxy-D-Glucose Positron Emission Tomography; HIT: Heavy Ion Therapy; LEM: Local Effect Model; MRI: Magnet Resonance Imaging; RBE: Relative Biological Effectiveness; RECIST: Response Evaluation Criteria in Solid Tumors
